#### 4.1.1. Study Schematic

The study schematic for the full study is provided in Figure 4-1.

**Figure 4-1. Study Schematic**

[figure not shown]

EOS = End of Study; PK = pharmacokinetic

Subjects will be admitted to the clinical research unit (CRU) and randomized to a treatment sequence on Day -1. For treatment sequence AB, Treatment 1 will be Treatment A and Treatment 2 will be Treatment B; for treatment sequence BA, Treatment 1 will be Treatment B and Treatment 2 will be Treatment A. Dosing schematics for Treatment A (GTX-104 IV administration) and Treatment B (oral nimodipine) are provided in [Figure 4-2](#) and [Figure 4-3](#), respectively. In each dosing period, study drug administration will begin at approximately 8 AM in fasted status. The 72-hour dosing period will end on Day 4 for the first treatment and Day 11 for the second treatment, at 4 AM (oral nimodipine) or 8 AM (GTX-104). The washout period will be at least 96 hours. EOS assessments will begin after the final PK assessments of the second treatment period. A detailed study assessment schedule is provided in [Table 4-1](#).

Note that the overall study days provided in the figure assume the minimum washout period of 96 hours. The washout period may be extended as long as study drug initiation occurs at the same time of day (approximately 8 AM). If the washout period is extended, the overall numerical study day for Treatment 2 and the EOS assessments will be different than those presented above.

Nimodipine will be administered based on each subject's randomized treatment schedule: AB or BA, where Treatment A is GTX-104 administered as a 72-hour continuous infusion at 0.15 mg/h in addition to 4 mg administered over 30 minutes q4h (total drug infused over 30 minutes every 4 hours = 4.075 mg, and total drug infused every 4 hours = 4.6 mg), and Treatment B is 60 mg oral nimodipine administered q4h for 72 hours (18 total doses).

The schematic outline for GTX-104 administration (Treatment A) is given in Figure 4-2. For GTX-104 infusion, the 4 mg dose will be administered at the same time as the start of the continuous infusion on Day 1 of the dosing period. The end of the continuous 0.15 mg/h infusion will be 8 AM on Day 4 of the study dosing period. Note that if GTX-104 is given as Treatment 2, and if the washout period is the minimum time, Day 1, 2, 3, and 4 of the dosing period will correspond to overall Study Days 8, 9, 10, and 11. The washout period may be extended as long as study drug initiation occurs at the same time of day (approximately 8 AM). If the washout period is extended, the overall numerical study day for Treatment 2 and the EOS assessments will be different than the aforementioned days.

The beginning of infusion on Day 1 should be administered after at least a 10-hour overnight fast, with breakfast provided 2 hours after the 8:00 AM dose (i.e., subjects fasted from 10:00 PM the night before to 10:00 AM). On Days 2-4, subjects need to be fasted between 2:00 AM-10:00 AM every day. Standardized meals will then be provided at approximately uniform times throughout the day, as described in Section 6.3. PK and clinical venous blood sampling should occur in the arm opposite to infusion, and the infusion line should not be used for PK sampling. For both Treatment A and Treatment B, oscillometric sphygmomanometer BP monitoring should occur prior to the first dose and 60 minutes post dose for the 8:00 AM, 12:00 PM, 4:00 PM, and 8:00 PM doses on Days 3 and 10, as specified in Table 4-1 and described in Section 8.10.

If Treatment A is given as Treatment 2, EOS assessments should be completed as described in Table 4-1 after the final PK blood sample collection.

**Figure 4-2. Study Drug Administration Schematic (Treatment A; GTX-104)**

[figure not shown]

EOI = end of infusion; IV = intravenous; q4h = every 4 hours

Note: In the event that Treatment A is given as the 2nd treatment after the minimum washout period, Day 1, 2, 3, and 4 will correspond to overall Study Days 8, 9, 10, and 11, respectively. The overall study days should be

adjusted if the washout period is longer. Note that this assumes the minimum washout period. The washout period may be extended as long as study drug initiation occurs at the same time of day (approximately 8 AM). If the washout period is extended, the overall numerical study day for Treatment 2 and the EOS assessments will be different than the aforementioned

The schematic outline for oral nimodipine administration (Treatment B) is given in Figure 4-3. Dosing with oral nimodipine should begin at approximately 8:00 AM on Day 1 of the dosing period at a dose level of 60 mg (two 30 mg capsules) q4h, with a total of 18 doses administered over the 72-hour dosing period. Note that if oral nimodipine is given as Treatment 2, and if the washout period is the minimum 96 hours, Day 1, 2, 3, and 4 of the dosing period will correspond to overall Study Days 8, 9, 10, and 11. The overall study days should be adjusted if the washout period is longer. The washout period may be extended as long as study drug initiation occurs at the same time of day (approximately 8:00 AM). If the washout period is extended, the overall numerical study day for Treatment 2 and the EOS assessments will be different than the aforementioned days.

The first dose of Day 1 should be administered after at least a 10-hour overnight fast, with breakfast provided 2 hours after the 8:00 AM dose (e.g., subjects fasted from 10:00 PM the night before to 10:00 AM). On Days 2-4, subjects need to be fasted between 2:00 AM- 10:00 AM every day. Standardized meals will then be provided at approximately uniform times throughout the day, as described in Section 6.3.

If Treatment B is given as Treatment 2, EOS assessments should be completed as described in Table 4-1 after the final PK blood sample collection.

**Figure 4-3. Study Drug Administration Schematic (Treatment B; Oral Nimodipine)**

[figure not shown]

q4h = every 4 hours

#### 4.1.2. Time and Events Schedule

**Table 4-1. Time and Events Schedule**

| Study Period
Overall Study Day                                    | Screening
-45 to -2 | Admission
-1 | Treatment 1 a
1 to 4 | Treatment Washout b
4 to 8 d | Treatment 2 a
8 to 11 d | End of Study
EOS/ET c
11 d |
|----------------------------------------------------------------------|------------------------|-----------------|------------------------------------|-------------------------------------------------------|--------------------------------------------------|--------------------------------------------------------|
| Informed consent                                                     | X                      |                 |                                    |                                                       |                                                  |                                                        |
| Subject ID number assignment                                         | X                      |                 |                                    |                                                       |                                                  |                                                        |
| Confirmation of eligibility                                          | X                      | X               |                                    |                                                       | X                                                |                                                        |
| Randomization                                                        |                        | X               |                                    |                                                       |                                                  |                                                        |
| Medical history & baseline demographics                              | X                      | X e  |                                    |                                                       |                                                  |                                                        |
| Prior medication assessment                                          | X                      | X               |                                    |                                                       |                                                  |                                                        |
| Full physical examination                                            | X                      |                 |                                    |                                                       |                                                  |                                                        |
| Brief physical examination                                           |                        | X               |                                    |                                                       |                                                  | X                                                      |
| Height measurement                                                   | X                      |                 |                                    |                                                       |                                                  |                                                        |
| Weight measurement                                                   | X                      | X               |                                    |                                                       |                                                  | X                                                      |
| Body mass index                                                      | X                      |                 |                                    |                                                       |                                                  |                                                        |
| 12-lead electrocardiogram                                            | X                      |                 |                                    |                                                       |                                                  | X                                                      |
| Vital signs g                                             | X                      | X               | X f                     | X                                                     | X f                                   | X                                                      |
| Orthostatic hypotension screen                                       | X                      | X               |                                    |                                                       |                                                  |                                                        |
| Clinical laboratory (chemistry, hematology, coagulation, urinalysis) | X                      | X               |                                    |                                                       |                                                  | X                                                      |
| Pregnancy test h                                          | X                      | X               |                                    |                                                       |                                                  |                                                        |
| COVID-19 virus test                                                  |                        | X i  |                                    | X j                                        |                                                  |                                                        |
| FSH test k                                                | X                      |                 |                                    |                                                       |                                                  |                                                        |
| Serology l                                                | X                      |                 |                                    |                                                       |                                                  |                                                        |
| HbA1c                                                                | X                      |                 |                                    |                                                       |                                                  |                                                        |
| CYP3A4 genotyping                                                    | X                      |                 |                                    |                                                       |                                                  |                                                        |
| Urine drug and alcohol screen                                        | X                      | X               |                                    |                                                       |                                                  |                                                        |
| Clinic admission                                                     |                        | X               |                                    |                                                       |                                                  |                                                        |
| Study drug administration                                            |                        |                 | X m                     |                                                       | X m                                   |                                                        |
| Standardized meals n                                      |                        |                 | X                                  |                                                       | X                                                |                                                        |
| Pharmacokinetic sampling o                                |                        |                 | X                                  |                                                       | X                                                |                                                        |
| Adverse events assessments                                           |                        |                 | ← Continuous →                     |                                                       |                                                  |                                                        |
| Concomitant medications                                              |                        |                 | ← Continuous →                     |                                                       |                                                  |                                                        |
| Clinic discharge                                                     |                        |                 |                                    |                                                       |                                                  | X                                                      |

CYP = cytochrome P450; EOS = End of Study; ET = Early Termination; FSH = follicle-stimulating hormone; hbA1c = hemoglobin A1c; ID = identification

- a. For treatment sequence AB, Treatment 1 will be Treatment A (GTX-104) and Treatment 2 will be Treatment B (oral nimodipine); for treatment sequence BA, Treatment 1 will be Treatment B (oral nimodipine) and Treatment 2 will be Treatment A (GTX-104).
- b. Each treatment period should be separated by a minimum of 96 hours to allow for treatment washout; washout time will be different for subjects, depending on their assigned treatment sequence (see Section 6.3).
- c. End of Study (EOS) assessments should be attempted in the event of Early Termination (ET). If the subject consents, this should include a blood sample for pharmacokinetic (PK) analysis taken as soon as possible after the decision to withdraw has been made.
- d. Overall Study Day may vary depending on the length of the washout period. The washout period should be at least 96 hours and adjusted such that the first dose administration of treatment 2 starts at approximately 8 AM.
- e. Confirmation of medical history and update, if needed.
- f. On Days 1 and 8 vital signs should be recorded within 1 hour prior to the first dose. On Days 3 and 10, blood pressure should be at 1 hour post-dose (for both IV and oral dose) for the 8:00 AM, 12:00 PM, 4:00 PM 8:00 PM doses. Measurements should be performed as described in Section 8.10. The same arm is to be used for all BP determinations.
- g. Unless otherwise noted (i.e., Days 3 and 10, see “f” above), blood pressure measured approximately q12h while subjects are in-clinic or before collection of PK blood samples, as appropriate.
- h. Serum pregnancy test ( $\beta$ -human chorionic gonadotropin [ $\beta$ -hCG]) for female subjects of childbearing potential.
- i. COVID-19 virus test to be collected within 5 days of CRU admission.
- j. COVID-19 virus test to be collected in the morning of Day 4 and on Day 7 on admission, with results to be available by Day 8, start of Period 2.
- k. For postmenopausal female subjects.
- l. Human immunodeficiency virus (HIV), hepatitis C (HCV), and hepatitis B surface antigen (HBsAg); will be tested at Screening only.
- m. Based on subjects’ randomized treatment sequence (AB or BA) GTX-104 or oral nimodipine should be administered as described in Section 4.1.1 and Section 6.2. GTX-104 administration will be a 30-minute infusion of 4 mg every 4 hours (q4h) in addition to the continuous infusion of 0.15 mg/h; nimodipine capsules will be administered orally with 240 mL of water at a dose level of 60 mg (two 30 mg capsules) q4h for 72 hours. For Treatment A, the continuous infusion will be completed at 72 hours post-start of infusion (approximately 8 AM on the fourth day of the treatment period); no 4 mg dose will be given at 72 hours.
- n. Meals and water should be provided during dosing as described in Section 6.3.1.
- o. Blood samples for PK analysis should be taken based on the treatment. For GTX-104 (Treatment A), samples should be taken on the first day of Treatment A, Pre-dose (time 0, before the 1st [8 AM] dose), and at 0.33, 0.5, 0.75, 1, 1.33, 2, 3, and 4 hours post initial (8 AM) dose, and starting on the third day at 48 (prior to initiation of the 4 mg dose), 48.33, 48.5, 48.75, 49, 49.33, 50, 51, 52, 52.33, 52.5, 52.75, 53, 53.33, 54, 55, 56, 56.33, 56.5, 56.75, 57, 57.33, 58, 59, 60, 60.33, 60.5, 60.75, 61, 61.33, 62, 63, 64, 64.33, 64.5, 64.75, 65, 65.33, 66, 67, 68, 68.33, 68.5, 68.75, 69, 69.33, 70, 71, 72-hours post-start of 1st infusion. PK and clinical venous blood sampling should occur in the arm opposite to infusion, and the infusion line should not be used for PK sampling. Note, for timepoints that are scheduled at the same time as the 4 mg dose (0, 48, 52, 56, 60, 64, 68, and 72 hours post-start of infusion), blood for PK analysis should be taken before initiation of the 30-minute infusion. For the 0.5, 48.5, 52.5, 56.5, 60.5, 64.5, and 68.5-hour timepoints, blood samples for PK analysis should be collected after completion of the 4 mg infusion. For oral nimodipine (Treatment B), PK samples taken for the 72-hour oral dosing period, listed sequentially, samples should be taken on the first day of Treatment B: Pre-dose (time 0, before the first [8 AM] dose), and at 0.33, 0.5, 0.75, 1, 1.33, 2, 3, and 4 hours post-dose, and on the third day blood samples for PK should be taken at: 48 (prior to initiation of the 8 AM 60 mg dose), 48.33, 48.5, 48.75, 49, 49.33, 50, 51, 52, 52.33, 52.5, 52.75, 53, 53.33, 54, 55, 56, 56.33, 56.5, 56.75, 57, 57.33, 58, 59, 60, 60.33, 60.5, 60.75, 61, 61.33, 62, 63, 64, 64.33, 64.5, 64.75, 65, 65.33, 66, 67, 68, 68.33, 68.5, 68.75, 69, 69.33, 70, 71, 72-hours since the first dose. Note, for timepoints that are scheduled at the same time as the 60 mg oral dose (48, 52, 56, 60, 64, 68, and 72 hours since first dose), blood for PK analysis should be taken before oral dose intake. See Section 8.11 for PK sampling schedule separated by Day and treatment.

In the event of ET, a blood sample for PK analysis should be taken as soon as possible after the decision to withdraw, if the subject consents.

## **4.2. Scientific Rationale for Study Design**

This is a standard crossover study designed to evaluate the relative BA at steady state of two formulations of nimodipine: GTX-104 (nimodipine for IV infusion; test formulation) and nimodipine oral capsules, RS (reference formulation). A crossover design was selected to reduce the impact of inter-subject variability in PK analysis. The design is in accordance with the most current guidance from the U.S. Food and Drug Administration (FDA), [FDA Bioavailability Studies Submitted in NDAs or INDs — General Considerations: FDA Guidance for Industry, 2019](#).

The washout period of at least 96 hours was selected based on the half-life of nimodipine to limit the possibility of study drug carryover effects.

## **4.3. Study Procedures**

*Note: Written informed consent must be obtained prior to performing any study-related procedure, including subject identification (SID) number assignment and Screening evaluations.*

### **4.3.1. Screening (Study Day -45 to Day -2)**

All study candidates will be screened to assess eligibility for enrollment into the study. A Screening Log will be maintained for all consented study candidates. Screen Failures, as defined in Section 5.3, will have the study candidate's unique SID (assigned as described in Section 8.2), date screened, and reason(s) for screening failure captured by electronic data capture (EDC).

During Screening, procedures and assessments will be performed and recorded as detailed in the Time and Events Schedule ([Table 4-1](#)).

COVID-19 virus testing will be performed on all study candidates after Day -5.

### **4.3.2. CRU Admission (Day -1)**

Subjects will be admitted to the CRU on the day prior to dosing. Eligibility will be reconfirmed as described in Table 4-1. Subjects will be randomized at admission, as described in Section 6.4. Any AEs that occur prior to study drug administration will be recorded as medical history. Thermometer reading will be done on Day -1. Any subject whose temperature is elevated ( $>100.2^{\circ}\text{F}$ ;  $37.9^{\circ}\text{C}$ ) will not be admitted to the CRU.

### **4.3.3. Treatment Period (Day 1 to 11)**

#### **4.3.3.1. Study Drug Administration (Days 1 to 11)**

*Note: The overall study days provided assume the minimum washout period, which must be at least 96 hours. However, the washout period may be extended as long as study drug initiation occurs at the same time of day (approximately 8 AM). A washout of 96 hours must occur even if the Day 1 must be repeated, as described in [Table 8-2](#). If the washout period is extended beyond the minimum, the overall numerical study day for Treatment 2 and the EOS assessments will be different than those described in this section.*

The treatment period will begin at first study drug administration on Day 1. The treatment period for each subject will be comprised of two 72-hour treatment periods, separated by a minimum 96-hour washout, with study drug administered according to the subject's

treatment sequence (AB or BA). The treatment period will be completed at final CRU discharge (approximately Day 11).

All study procedures will be conducted as described in the Time and Events Table ([Table 4-1](#)). On Days 1 to 4 of each treatment period (Days 1 to 4 for the first treatment and approximately Days 8 to 11 for the second treatment), study drug will be administered at the same time each day (starting at approximately 8 AM on Day 1). Each morning (4 AM and 8 AM) doses will be administered in fasted status, and breakfast will be provided 2 hours after the 8 AM dose (e.g., subjects should be fasted from 2 AM to 10 AM). On Day 1, since the first dose is at 8 AM, subjects can be fasted overnight and get the first breakfast at 10 AM, 2 hours after the first dose.

Standardized meals will then be provided at approximately uniform times throughout the day, such that the 4 AM, and 8 AM doses (e.g., the oral dose or the 4 mg infusion for GTX-104) for each treatment are administered to subjects in the fasted state, and other doses (12 PM, 4 PM, 8 PM and 12 AM) were given in fed status each day. On Days 3 and 10 only, water will be restricted 30 minutes before and 1 hour after administration of both IV and oral doses. Outside of these windows, water will be allowed *ad libitum*. Water will be administered with study drug, and 1 hour before and after initiation of infusion for Treatment A. Outside of this window, water will be allowed *ad libitum*.

For both Treatment A and Treatment B, baseline (prior to first dose) BP determination will be taken via oscillometric sphygmomanometer. On Days 3 and 10, 1 hour post dose BP determinations will be performed after the 8:00 AM, 12:00 PM, 4:00 PM and 8:00 PM doses, as described in [Section 8.10](#).

Any new AEs that occur after treatment administration will be attributed to the formulation administered in that dosing period. Any new AEs that occur during washout will be attributed to the treatment administered during the first dosing period.

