### **3.3. Safety Endpoints**

Safety endpoints will include:

- Incidence of treatment-emergent AEs (TEAEs) and SAEs, grouped by system organ class, preferred term, relationship to study drug, severity, and treatment regimen
- Change from baseline in clinical laboratory evaluations (hematology, clinical chemistry, and urinalysis), vital signs, physical examination results, and 12-lead safety ECG parameters at the end of the study

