## **8.4. Physical Examinations**

Physical examinations will be completed as described in the Time and Events Schedule ([Table 4-1](#)). A complete physical examination will be performed at Screening, including assessments of the skin, head, eyes, ears, nose, throat, neck, thyroid, lungs, heart, abdomen, lymph nodes, extremities, height, and weight, and a limited neurological examination. The physical examination will not include a pelvic, breast, or rectal exam.

An abbreviated physical examination including assessment of skin, peripheral pulses, lungs and heart will be performed on admission to the CRU, and at the end of the subject's study participation (EOS or ET). Additional assessments may be performed at the discretion of the Investigator. Any significant physical examination finding at Screening should be recorded in the subject's medical history. If any clinically significant change is noted from Screening, it will be reported as an AE and will be followed up to resolution or upon reaching a stable end point.

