#### **8.9. Clinical Laboratory Evaluations**

All laboratory tests will be performed on-site, by the laboratory affiliated with the Phase 1 unit. Blood and urine for clinical laboratory testing prior to enrollment will be collected after an overnight fast (at least 8 hours) and will include evaluations summarized in [Table 8-1](#).

Venous blood will be drawn for the tests listed in [Table 4-1](#). Because of the large number of samples to be collected, repeated venipuncture should be minimized, as well as long-term indwelling catheters. Ideally, venipuncture will be performed for Day 1 PK samples. On Day 2, only any required infusion line should be in place. On Day 3, an indwelling large gauge catheter should be placed for sample collection in the contralateral arm from any infusion line.

Subjects will be in a seated or semi-reclined position during blood collection.

Any abnormal hematology, serum chemistry, or urinalysis test result deemed CS by the Investigator will be reported as an AE and repeated, including test results obtained at EOS/ET. Repeat analyses will be performed until resolution, or until the Investigator determines that resolution of the laboratory abnormality is not expected.

If blood samples for clinical laboratory tests are scheduled to be collected at the same time as an ECG or vital signs, the ECG and/or vital signs must be obtained before the blood sample collection as drawing blood may affect the vital signs.

The total volume of blood collected for clinical laboratory tests from each subject is not expected to exceed 60 mL over the study (not including repeat laboratory tests, should these be necessary). See [Appendix 1](#) for the estimated total volume of blood collected from each subject over the course of the study.

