### **10.6. Safety Analysis**

All safety data will be listed by subject. TEAEs will be summarized for each treatment by system organ class, preferred term, severity, and relationship to test article. Observed values and changes from baseline for clinical laboratory test data, safety ECGs, physical examination results, and vital signs will be summarized using appropriate descriptive statistics. Potential future analyses will be detailed in a standalone SAP. The Safety Population will be used.

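### Clinically significant lab, ECG or exam findings first seen at End of Study follow both treatments in completers, yet the attribution rule puts them by default in the second treatment's adverse event counts

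*Protocol*

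**What the plan says.** **Schedule.** Table 4-1 places clinical laboratory tests at Screening, Admission and EOS. The row "12-lead electrocardiogram" is marked at Screening and EOS only, and the brief physical examination at Admission and EOS only. None of the three is scheduled in Treatment 1, the washout or Treatment 2. Sections 4.1.1 and 4.3.4 put EOS after the last PK sample of the second period.

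**Endpoints and summaries.** Section 3.3 groups adverse events by treatment regimen, among other factors. Its second safety endpoint is change from baseline in laboratory evaluations, "vital signs, physical examination results, and 12-lead safety ECG parameters at the end of the study". Section 10.6 says "TEAEs will be summarized for each treatment by system organ class, preferred term, severity, and relationship to test article".

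**When a finding becomes an adverse event.** Section 8.9 says that a clinically significant hematology, chemistry or urinalysis result "will be reported as an AE and repeated, including test results obtained at EOS/ET". Sections 8.4, 8.7 and 9.4 do the same for examination changes, ECGs and abnormal assessments in general.

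**Attribution.** Section 4.3.3.1 has two sentences. The first is "Any new AEs that occur after treatment administration will be attributed to the formulation administered in that dosing period". The second is "Any new AEs that occur during washout will be attributed to the treatment administered during the first dosing period". Section 9.1.1 defines treatment emergence against one study baseline, before the first dose of any study drug, so there is no separate baseline for Period 2.

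**The concern.** The attribution rule works only if the onset of an event can be placed in a period. For symptoms and vital signs it can, because subjects are observed throughout both periods. For laboratory, ECG and examination findings it cannot, because a completer has no scheduled reading between the two treatments. An abnormality caused in Period 1 and still present at EOS looks the same as one that arose in Period 2. It would enter the by-treatment table under the second drug.

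The secondary objective is the safety and tolerability of each product. The protocol itself lists relevant effects of nimodipine: ECG abnormalities and abnormal liver tests with the capsules (Section 1.2.2.1), and thrombocytopenia and transient liver enzyme increases with intravenous infusion (Section 1.2.2.2). For these findings, a by-treatment count would suggest an attribution that the data cannot support.

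**Working it through.** The plan states no figure on this point, so there is none to reproduce. The check is the schedule above plus a short derivation.

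**Inputs from the protocol**
- Allocation 1:1 to AB or BA (Section 6.4).
- At least 50 completers (Section 10.2), taken as 25 per sequence.
- Period 1 ends on Day 4 and EOS is on Day 11 with the minimum washout (Section 4.1.1), so a Period 1 abnormality must last about 7 days to be seen.

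**Assumptions (the protocol gives no values)**
- pA and pB: probabilities that GTX-104 (A) or the capsules (B) cause a clinically significant abnormality.
- s: share of Period 1 abnormalities still present at EOS.
- The two causes act independently, and a Period 2 abnormality is present at EOS.

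**Formulas.** A finding at EOS goes to the Period 2 drug.
- Sequence AB, charged to B: 1 − (1 − pB)(1 − s·pA)
- Sequence BA, charged to A: 1 − (1 − pA)(1 − s·pB)

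Subtracting the first from the second, the s·pA·pB terms cancel:

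A − B = pA − pB − s(pA − pB) = (1 − s)(pA − pB)

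This uses the 25 Period 2 subjects per treatment as denominator. If all 50 subjects exposed to each treatment are the denominator, the counts stay the same and the difference is half as large.

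**Example: pA = 10%, pB = 2%, true difference 8.0 points**

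| s | Charged to A (of 25) | Charged to B (of 25) | Difference, Period 2 denominator | Difference, all 50 exposed |
|---|---|---|---|---|
| 0 | 10.0% (2.50 events) | 2.0% (0.50) | 8.0 points | 4.0 points |
| 0.25 | 10.45% (2.61) | 4.45% (1.11) | 6.0 | 3.0 |
| 0.5 | 10.9% (2.72) | 6.9% (1.73) | 4.0 | 2.0 |
| 0.75 | 11.35% (2.84) | 9.35% (2.34) | 2.0 | 1.0 |
| 1 | 11.8% (2.95) | 11.8% (2.95) | 0.0 | 0.0 |

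Assumed incidences of 20% and 5% give the same ratios: the true 15.0 points become 7.5 at s = 0.5 and 0 at s = 1 on the Period 2 denominator.

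**Where the events go if only A causes them.** Half of the A-caused abnormalities arise in Period 1 of sequence AB. Of all A-caused events, a share s/2 is charged to B and (1 − s)/2 is never seen. At s = 1 that is one half charged to B and none unseen; at s = 0, none and one half; at s = 0.5, one quarter each.

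**At an incidence nearer the protocol's own.** Section 1.2.2.1 gives abnormal liver tests in 0.4% to 1.2% of patients on capsules. Taking 1.2% for one treatment and 0 for the other, the true expected count in 50 subjects is 50 × 0.012 = 0.6 against 0. At s = 1 the table would show 25 × 0.012 = 0.3 against 0.3.

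**The case against.** - **The rule speaks of when events occur, not when they are found.** Sections 9 and 9.2 require an onset date and time for each event. This stands as a reading of the words. It does not solve the problem, because without an earlier reading the investigator has nothing to date the onset by, and the protocol gives no rule for unknown onset.
- **Only clinically significant findings become adverse events.** This stands and limits the point. A reader might infer that every abnormal value at EOS is charged to the second drug; Sections 8.4, 8.7, 8.9 and 9.4 do not say so.
- **Long persistence is unlikely.** The washout was chosen from the half-life to limit carryover (Section 4.2), and the liver enzyme rise cited for infusion is transient (Section 1.2.2.2). This makes s near 1 hard to defend, especially for ECG changes. At s = 0 there is no bias on the Period 2 denominator.
- **Events will be few.** This stands. At the protocol's own rates, a table of 50 to 60 subjects could hardly show a difference under any rule.
- **No by-treatment comparison of laboratory or ECG change is promised.** This also stands. Sections 3.3 and 10.6 tie treatment to the adverse event summary only, and Section 10.1 leaves safety summary methods to an SAP that has primacy. But the attribution rule and the by-treatment adverse event tables are fixed in the protocol itself.
- **The sparse schedule was deliberate.** Appendix 4 records that on-treatment ECGs were judged unnecessary in healthy subjects. That answers whether to measure more, not how to attribute what is found at EOS.

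**Conclusion.** The point holds within limits. For completers, the protocol's default charges the second treatment with any clinically significant laboratory, ECG or examination finding first detected at EOS, although its period of onset is unknown. The attributed difference is (1 − s) times the true one on the Period 2 denominator, and half of that if all exposed subjects are counted. The incidences and s are assumptions.

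A reader might infer that the rule erases any difference between the products. The documents do not support that: it would need every Period 1 abnormality to last about 7 days. A reader might also infer that a GTX-104 effect would be half unseen and half charged to the capsules at once. The shares (1 − s)/2 and s/2 add up to one half, so this cannot happen at any s.

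Symptomatic adverse events, vital signs and the PK endpoints are unaffected. The change is worth making because the rule is stated in the protocol and correcting it costs almost nothing.

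**What to change.** Amend the wording of Sections 4.3.3.1, 3.3 and 10.6 as follows.

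1. Exempt clinically significant laboratory, ECG or physical examination findings first detected at EOS, in subjects who received both treatments, from the period-attribution rule, unless an unscheduled test dates their onset.
2. Report these findings, and the EOS change from baseline, by sequence and overall, labelled as following both treatments and kept out of the by-treatment adverse event tables.
3. For subjects who terminate early in Period 1, keep attribution to the one treatment received.

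This needs no new procedure, visit or blood sample. The cost is slightly more table work and fewer events in the by-treatment tables.

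I would not add a laboratory panel at the end of Period 1. It would leave ECG and examination findings unresolved, and an on-treatment value is a poor baseline for Period 2. By Appendix 1 it would also raise clinical laboratory blood from 25.5 + 12 + 8.1 = 45.6 mL to 45.6 + (8.5 + 4.0 + 2.7) = 60.8 mL, above the 60 mL expected in Section 8.9.
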